**Methods and Analysis:**

This is a sham-controlled, randomized clinical trial. A total of 180 subjects will be randomly allocated to either the ETN group or the sham ETN group. Treatment will be administrated three times a week for four consecutive weeks, with a 6-month follow-up. The primary outcome measure will be the Numerical Rating Scale for neck pain (NRS-NP) over a period of the 4 weeks. Secondary outcome measures include the Northwick Park Neck Pain Questionnaire (NPQ), Neck Disability Index (NDI), Patient Global Impression of Change (PGIC), patient expectation, and preference assessment. The chi-square test or Fisher's exact test will be used for proportions of participants having clinically meaningful improvement. Analysis of covariance or repeated-measures analysis of variance will be applied to examine changes in the outcome measures from baseline.

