### Outcome Measures

#### Primary Outcome and Measurement

The primary outcome of this trial will be the proportion of participants with at least 50% decrease from baseline in the score of NRS-NP at the 4th week (25). The NRS-NP is a valid and reliable 11-point rating scale to assess the average intensity of neck pain during the last 3 days (26, 27). It is sensitive to small changes with a lower failure rate and can be delivered either graphically or verbally (26–28). The score of NRS-NP ranges from 0 (i.e., no pain at all) to 10 (i.e., the worst pain imaginable). Participants will be asked to circle out 1 of the 11 numbers to describe their pain. The scores of NRS-NP can be categorized into four degrees: 0 (i.e., no pain), 1–3 (i.e., mild), 4–6 (i.e., moderate), and 7–10 (i.e., severe). The reduction of 50% from baseline is regarded as golden standard of the NRS-NP to interpret significant clinically improvement (15, 28, 29).

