#### Secondary Outcomes

Secondary outcomes include the proportion of participants with an at least 50% decrease from baseline in NRS-NP score at the 16th and 28th weeks; the changes from baseline in NRS-NP score at the 4th, 16th, and 28th weeks; and the proportion of participants with an at least 30% decrease from baseline in NRS-NP at the 4th, 16th, and 28th weeks. Other secondary outcomes include:

Changes in the Northwick Park Neck Pain Questionnaire (NPQ) percentage score from the baseline at the 4th, 16th, and 28th weeks.The proportion of participants with an at least 25% decrease in NPQ percentage score together with a “better” or “much better” at the 4th, 16th, and 28th weeks.

The NPQ is a validated questionnaire to assess the overall symptoms of neck pain (30). It contains 9 questions, the score of each ranging from 0 to 4, on the aspects of intensity, duration, numbness, sleep disturbance, and disability in carrying, watching television, working, social life, and driving. The total score of the 9 questions will be converted to NPQ percentage score (divided by 36 for people who drive and by 32 for those who do not), which ranges from 0 to 100%, and with higher scores indicating worse condition. A 25% decrease in NPQ percentage score and a “better” or “much better” for the 5-scale global effectiveness rating are both needed (31) to reach Minimal Clinically Important Difference (MCID).

(3) Changes from the baseline in Neck Disability Index (NDI) score at the 4th, 16th, and 28th weeks.(4) The proportion of participants with an at least 10-point decrease from the baseline in NDI score at the 4th, 16th, and 28th weeks.

The NDI is a frequently used instrument to evaluate the self-reporting functional status of patients with neck pain. It consists of 10 items concerning pain, headache, concentration, and daily obligatory activities. Each section is scored with an ordinal scale from 0 to 5, with a maximum score of 50 points (32, 33). Higher scores indicate greater functional limitation. The NDI has been translated into the simplified-Chinese version, which has been shown to have reproducibility, reliability, and validity (34). A 10-point decrease is required to achieve clinically important meaning (27, 35–37).

(5) The proportion of participants reported “much improved” or “very much improved” on Patient Global Impression of Change (PGIC) at the 4th week.

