### Statistical Analysis

Data calculation will be performed using the SPSS software Ver.20.0 under the ITT principle. Baseline data before intervention will be analyzed to see if the two groups are comparable. The continuous data will be represented as mean ± SD deviation or median [interquartile range (IQR)]. Proportions of participants having clinically meaningful improvement will be analyzed using chi-square test or Fisher's exact test. Changes in the outcome measures from the baseline will be examined by using analysis of covariance for normally distributed data to exclude the possible impact on the effect by covariates of gender and work habits. Repeated-measures analysis of variance will be used if the data are not normally distributed. The Cochran-Mantel-Haenszel test will be used to analyze categorical data, which will be represented by percentages and case. We will use linear regression to discuss the association of participants' expectations and the treatment. Missing research data will be imputed by multiple imputations. For all statistical calculation, the significance level will be two-sided and set at 0.05. A *p* < 0.05 will be considered to indicate statistical significance.

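### The fallback for non-normal secondary outcomes, repeated-measures ANOVA, itself assumes normal errors and can change which treatment comparison is reported

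*Protocol article*

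**What the plan says.** The Statistical Analysis section of the Protocol article sets a two-branch rule for the change scores. If the data are normal: "Changes in the outcome measures from the baseline will be examined by using analysis of covariance for normally distributed data". The stated purpose of that model is "to exclude the possible impact on the effect by covariates of gender and work habits". If they are not: "Repeated-measures analysis of variance will be used if the data are not normally distributed". The section names no transformation, rank method or bootstrap for these outcomes.

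The abstract gives the same pair of methods as alternatives, without a condition: "Analysis of covariance or repeated-measures analysis of variance will be applied to examine changes in the outcome measures from baseline".

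The outcomes concerned are all listed under Secondary Outcomes, each with three time points, for example "the changes from baseline in NRS-NP score at the 4th, 16th, and 28th weeks" and "Changes from the baseline in Neck Disability Index (NDI) score at the 4th, 16th, and 28th weeks". NPQ percentage score has the same three weeks.

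**The concern.** A fallback for non-normal data should need a weaker distributional assumption than the method it replaces. Repeated-measures ANOVA does not. It is a linear model with normal errors, as ANCOVA is, and its within-subject tests need sphericity as well.

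The rule also joins two unrelated choices. Whether to model one visit or all visits together is a question about the treatment comparison. Whether the errors are normal is a question about distribution. When the second decides the first, the reported comparison depends on the shape of the data. NRS-NP might be reported as a difference at each week and NDI as an effect across weeks, and the reader could not set the two side by side.

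**Working it through.** The plan gives no figure for this rule, so there is none to reproduce. The check compares the two branches and then illustrates how far apart they can be.

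**Inputs from the Protocol article**
- Methods and covariates: Statistical Analysis.
- Outcomes and weeks: Secondary Outcomes. 3 scales x 3 weeks = 9 change comparisons.
- NRS-NP is an 11-point scale from 0 to 10 (Primary Outcome and Measurement), with entry at 4 or more (Inclusion Criteria).
- 90 per group with 20% dropout allowed (Sample Size): 90 x (1 - 0.20) = 72 completers per group.

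**Step 1. Assumptions.**

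| | ANCOVA (normal branch) | Repeated-measures ANOVA (non-normal branch) |
|---|---|---|
| Normal errors | assumed | assumed |
| Sphericity | not needed | needed for within-subject tests |
| Covariates stated | gender, work habits | none stated |
| Treatment comparison | adjusted group difference in the change analysed | not named (group or group-by-time) |

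The second branch relaxes nothing that the first one requires.

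**Step 2. What each branch estimates.** Suppose the true reductions in NRS-NP against sham are 1.0, 0.5 and 0 points at weeks 4, 16 and 28 (an assumption).
- Difference at week 4: 1.0.
- Group main effect on the changes: (1.0 + 0.5 + 0)/3 = 0.5.
- Group-by-time, week 28 against week 4: 0 - 1.0 = -1.0, which measures loss of effect, not benefit.

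With a constant effect of 1 point, the week-4 difference and the main effect are both 1.0, and the group-by-time contrast is 1.0 - 1.0 = 0.

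**Step 3. Illustrative simulation.** 3,000 runs per scenario, 72 per group, complete data. Scores are right-skewed integers bounded at 0 and 10, with baseline at least 4. These distributions are assumed, because the article gives no SDs. ANCOVA at week 4 adjusts for baseline score. The repeated-measures main effect is the unadjusted group comparison of each participant's mean change over the three weeks.

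| True reductions at weeks 4, 16, 28 | ANCOVA week 4: mean estimate (rejects) | Repeated-measures main effect: mean estimate (rejects) |
|---|---|---|
| 0, 0, 0 | 0.00 (4.9%) | 0.00 (5.1%) |
| 1.0, 0.5, 0 | -0.97 (91%) | -0.48 (68%) |
| 1, 1, 1 | -0.97 (90%) | -0.97 (99.9%) |

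The Monte Carlo standard error at 5% is sqrt(0.05 x 0.95/3000) = 0.004, so 4.9% and 5.1% cannot be told apart from 5%.

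**Step 4. Does the fallback cure the trigger?** In these data a Shapiro-Wilk test rejected normality of the week-4 changes in 100% of runs. It also rejected for the repeated-measures residuals (at one or more weeks) in 100% of runs. The data that trigger the switch violate the second model's assumption as well.

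**Limits of the simulation.** It did not study the group-by-time test or a failure of sphericity. The gap in rejection rates in the second scenario partly reflects the baseline adjustment, which only the ANCOVA had.

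**The case against.** Several points on the other side stand.

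- **Scope.** The primary outcome is the proportion with at least a 50% fall in NRS-NP at week 4. It is tested by chi-square or Fisher's exact test, and the sample size rests on it. A reader might infer that the trial's main conclusion is at risk; nothing in the article supports that.
- **Robustness.** With 72 to 90 per group, ANCOVA and the between-group repeated-measures comparison both tolerate non-normality well. A reader might infer an inflated false-positive rate; the simulation shows none for these two tests.
- **Silence.** A reader might infer that gender and work habits are dropped in the second branch, or that the main effect is what would be reported. The article does neither: it attaches the covariates to the ANCOVA sentence and is silent about the other model. Repeated-measures ANOVA with the same covariates and week-specific contrasts would match the ANCOVA comparison.
- **Which branch applies.** A reader might infer that bounded pain scores will almost surely fall into the non-normal branch. The article gives no distributions, so the 100% rejection above only reflects the skewed scores assumed.
- **Blinding.** The statisticians are blinded and allocation is revealed only after the analysis (Blinding; Data Management and Quality Control). This limits choosing a method because it favours one group.

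None of this makes the fallback suitable. Blinding does not stop different scales from taking different branches, and robustness means that the switch brings no benefit. The rule is stated text, not a detail left to an analysis plan.

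**Conclusion.** The point holds at moderate severity. The stated fallback does not address the condition that triggers it, because it rests on normal errors too. The switch leaves the method and the treatment comparison open for the nine secondary change results.

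The comparisons separate only if the effect varies over the three weeks and no week-specific contrast is used; under a constant effect the mean estimates agree (-0.97 and -0.97). A varying effect is plausible here: follow-up runs for six months, and the Introduction reports that TENS did not differ significantly from sham, especially at long-term follow-up. The sizes quoted depend on assumed score distributions and effects. The primary outcome, its test and the sample size are not affected, and the harm is not a raised type I error.

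**What to change.** 1. In Statistical Analysis, delete the switch that depends on normality, and align the abstract sentence.
2. Prespecify one method for all changes in NRS-NP, NPQ and NDI. Either of these would do:
   - ANCOVA at each week, adjusted for baseline score, gender and work habits; or
   - a mixed model for repeated measures with the same covariates, treatment, visit, treatment-by-visit and week-specific contrasts.
3. Report the between-group difference with its 95% CI at weeks 4, 16 and 28.
4. Address non-normality with a rank-based or bootstrap sensitivity analysis that does not replace the main result.
5. State how the chosen model works with the multiple imputation already planned.

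The simpler option, ANCOVA throughout, is enough to cure the defect. The cost is a few sentences and slightly more analysis work. No new data, visits or participants are needed. The change should be made before allocation is revealed, and preferably before the outcome distributions are inspected.

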## Discussion

The objective of this study is to evaluate the efficacy and safety of ETN therapy for non-specific chronic neck pain. Demographic characteristics will be collected including age, duration, job, psychosocial or physical risk factors, level of exercise, history of injury, and history of autoimmune disease. The outcomes are designed in accordance with the Initiative on Methods, Measurement, and Pain Assessment in Clinical Trials (IMMPACT) recommendations for core outcomes of chronic pain (41). Both the reduction of 30 and 50% on NRS are applied as outcome measures in this trial. Although the reduction of 30% from baseline in NRS is consistently acknowledged as MCID in current studies (15, 23, 25, 27, 28), a 50% reduction is widely used in clinical trials as a rigorous outcome measurement interpreting more significant improvement in symptoms (15, 28, 29). Additionally, multiple outcomes will be evaluated, as various as pain intensity, disability, quality of life, and the degree of subjective satisfaction.

The effectiveness of both manual acupuncture and TENS has been identified by previous studies (15, 42) in reducing chronic neck pain. Since ETN treatment has been an integration of thumbtack needling and electric stimulation, the treatment effect will probably be stronger and comprehensive. Notably, it is easy to administrate thumbtack needles on acupoints, even by patients themselves at home.

In this trial, blunt-tip thumbtack needle with no penetration and transient minimal electric stimulation is designed as sham control. It can produce acupuncture-like sensation of tingling or pain by pressing the blunt tip on acupoints without skin penetrating, similar to the validated placebo needle (43, 44). To maintain the success of blindness, participants from different groups will be avoided to contact with each other. The outcome assessor and the statistician will also be concealed to group allocation. These approaches are constructed to reduce possible biases attached to the results.

Limitations of this study are as follows. Group allocation will be not blinded to the acupuncturist, whose attitude for or against an intervention might be inevitably transferred to participants. Besides, this study does not implement a waitlist control in consideration of ethics principles, in which condition we cannot exclude the influence of spontaneous remission of disease.

This prospective trial will evaluate the efficacy and safety of ETN for chronic neck pain and provide evidence for clinical health recommendations.

## Ethics Statement

The studies involving human participants were reviewed and approved by the Research Ethical Committee of Guang'anmen Hospital, China Academy of Chinese Medical Sciences. The patients/participants provided their written informed consent to participate in this study.

